## Abstract

**Background:**

Interstitial lung diseases (ILDs), a group of parenchymal lung disorders, present with varying degrees of inflammation and fibrosis, which lead to symptoms such as progressive breathlessness, impaired quality of life (QoL), and reduced life expectancy. Patients with ILD can experience a sudden worsening of their condition, known as an acute exacerbation, which is associated with inappropriate hospital admissions, concomitant National Health Service (NHS) costs, impaired QoL, and high mortality. The heterogeneity of ILDs, the unpredictability of acute exacerbations, and significant variation in disease progression and response to treatment present numerous management challenges. Standard care typically involves 3-6 monthly hospital outpatient visits to monitor disease and assess response to treatment. Home monitoring with remote review of spirometry, pulse oximetry, and patient-reported measures offers an alternative approach to in-person clinic review and laboratory-based physiological measurements. Clinical trials indicate home monitoring of patients with ILD is acceptable, and results correlate with laboratory-based pulmonary function tests (PFTs). The impact of implementing home monitoring for patients with ILD in a real-world setting is not well understood.

**Objective:**

We aim to evaluate the safety, effectiveness, and acceptability of home monitoring with standard care in the management of patients with ILD.

**Methods:**

This study has been registered as a quality improvement project at Guy’s and St Thomas’ NHS Foundation Trust (reference 13660) and Royal Devon University Healthcare NHS Foundation Trust (reference 24-1378). The project has been co-designed by the steering group, including clinicians, researchers, technology partners, a patient advocacy charity, and patients diagnosed with ILD. Patients who meet the inclusion criteria will be provided a handheld spirometer, pulse oximeter, and access to patientMpower, an electronic health app, on their smart devices and followed up for 12 months. All participants will be asked to complete at least once weekly home spirometry and pulse oximetry measurements and 3 monthly patient-reported measures, including outcome, engagement, and experience measures, using the patientMpower app. Results will be available to the clinicians in real time and used to monitor disease progression, symptoms, and QoL, and to assess treatment response.

**Results:**

This study was funded by NHS Digital in September 2021. Patient recruitment and data collection started in March 2022. By January 2024, 186 patients were enrolled. All patients will have home monitoring for at least 12 months. Results are expected to be published at the end of 2025.

**Conclusions:**

We hypothesize home monitoring will be safe, effective and acceptable for patients with ILD and result in a 50% reduction in routine laboratory-based pulmonary function tests and in-person clinic consultations.

**International Registered Report Identifier (IRRID):**

DERR1-10.2196/65339

## Introduction

### Interstitial Lung Disease

Interstitial lung diseases (ILDs), a group of parenchymal lung disorders, present with varying degrees of inflammation and fibrosis [1]. Idiopathic pulmonary fibrosis (IPF) is the archetypal, invariably progressive, fibrotic lung disease characterized by a decline in lung function, worsening breathlessness, impaired quality of life (QoL), and reduced life expectancy [2,3]. Other ILD subtypes may develop into a progressive fibrotic phenotype despite conventional therapies and are described as progressive pulmonary fibrosis (PPF) [4]. Shared mechanistic and clinical features have been identified between PPF and IPF such as worsening respiratory symptoms, decline in lung function, and premature mortality [5-12]. The heterogeneity of ILDs, the unpredictability of acute exacerbations, and significant variation in disease progression and response to treatment present numerous challenges in diagnosis and management.

The gold standard for ILD diagnosis requires a multidisciplinary team, preferably an interdisciplinary team, an approach where experts, including respiratory physicians, rheumatologists, thoracic radiologists, pathologists, and ILD specialist nurses, review clinical symptoms, exposure history, serology, and radiology [4]. Frequent monitoring, including assessment of symptoms, functional capacity, and physiological measurements, is recommended to enable the identification of disease progression, assess response to treatment, and inform ongoing management [4,13]. The frequency of follow-up is determined by the severity of disease progression, deterioration in QoL, and available resources [4,14]. In-person clinic review often places a significant physical burden on patients due to exertional breathlessness, oxygen dependency, infection risk, work commitments, and the need for carer support. In the United Kingdom, many patients travel long distances with inadequate transport provision to reach ILD specialist services. Consequences include delayed follow-up and increased costs to the patient, the National Health Service (NHS), and the environment [15].

### Home Monitoring

Clinical trials have demonstrated that home spirometry is acceptable to patients with ILD [16-18]. Home spirometry correlates with clinical spirometry and is thought to be effective in detecting disease progression in patients with ILD [19,20]. The widespread increase in societal digitization, including smartphone utilization, has enabled the development of digital care pathways. The COVID-19 pandemic further accelerated the utilization of home monitoring devices, such as pulse oximeters, to support admission avoidance or early discharge from the hospital, shifting the emphasis to supporting the delivery of care closer to home [21,22]. Home monitoring of patients with ILD is not yet part of standard care, despite its perceived utility. This may be due to organizational factors, clinician workload, funding, patient factors including the ability to adopt digital technology, perceived risk to psychological well-being, and concerns regarding the correlation of home and laboratory-based pulmonary function tests (PFTs) [18,23,24].

Home monitoring, including spirometry, pulse oximetry, and patient-reported measures (PRMs), with remote review offers an alternative approach to in-person clinic review and laboratory-based PFTs for patients with ILD. It has the potential to support early identification of disease progression or acute exacerbation, assess response to treatment, enhance QoL, and alleviate health care burden [23]. Evidence of the long-term safety, effectiveness, and acceptability of home monitoring, including assessment of the impact on clinical outcomes, resource use, and patient satisfaction is needed to optimize this approach to patient care. We aim to assess if home monitoring is safe, effective, and acceptable for patients with ILD when offered in addition to standard care. We hypothesize home monitoring will lead to a 50% reduction in routine laboratory-based PFTs and in-person clinic consultations.

## Methods

### Study Design

This study has been co-designed using the ObsQual (Observational and Qualitative Study Protocol Reporting) checklist with a steering group of clinicians, researchers, technology partners, a patient advocacy charity, and patients with ILD [25]. All participants will be offered a portable handheld Spirobank Smart MIR spirometer and Nonin 3230 Bluetooth pulse oximeter. These will be linked to patientMpower, an electronic health app, downloaded to the patient’s smart device. The recruiting clinician will counsel the patient, provide written information, and gain informed patient consent. Trained clinicians will provide patient training on the use of the home spirometer, pulse oximeter, and completion of PRMs, in person or virtually.

Patients will be asked to record spirometry and pulse oximetry measurements at least once weekly, and a series of PRMs at baseline and at months 3, 6, 9, and 12. These include the idiopathic pulmonary fibrosis patient-reported outcome measure (IPF-PROM), modified Medical Research Council dyspnea scale (mMRC), EQ-5D-5L, cough severity visual analog scales (VAS),Global Rating of Change Questionnaire (GRCQ), 9-item Patient Health Questionnaire (PHQ-9), 7-item General Anxiety Disorder (GAD-7), and experience and engagement measures, including Porter-Novelli, a home spirometry satisfaction questionnaire (SpiroQ), and the interstitial lung disease patient-reported experience measure (modified from the rheumatoid arthritis patient-reported experience measure) [26-34]. These PRMs have been used and validated in IPF and PPF populations, except for SpiroQ, which was co-designed with the steering group to support us in measuring patient satisfaction with home monitoring. EQ-5D-5L is a health utility measure that will enable health economic evaluation [35]. The timeline of measurements is demonstrated in Figure 1. All data recorded via the app will be visible to the patient and the clinicians in real-time via a secure browser-based portal.

**Figure 1 figure1:**
[figure not shown]
Interstitial lung disease supported self-management schematic. PFTs included FVC, forced expiratory volume, diffusing capacity of the lungs for carbon monoxide, carbon monoxide transfer coefficient, and partial pressure of oxygen in the alveoli. PRMs include idiopathic pulmonary fibrosis patient-reported outcome measure, modified Medical Research Council dyspnea score, EQ-5D-5L, cough visual analogue scale, Global Rate of Change Questionnaire, SpiroQ (home spirometry satisfaction questionnaire), 9-item Patient Health Questionnaire, 7-item General Anxiety Disorder, Porter-Novelli, and modified patient-reported experience measure for patients with rheumatoid arthritis. 6MWT: 6-minute walk test; CPI: composite physiologic index; FVC: forced vital capacity; GAP: gender-age-physiology; HCP: health care professional; HRCT: high-resolution computed tomography; MDT: multidisciplinary team; PFT: pulmonary function test; PRM: patient-reported measure.

The registering clinician will be responsible for setting thresholds for a ≥10% decline in absolute forced vital capacity (FVC) and oxygen saturation <94%, according to the individual’s baseline measurement [34]. If measurements fall below the threshold, alerts will be sent to the clinical team via the browser-based portal. The clinical team will review daily alerts during weekday working hours (Monday to Friday, 9 AM-5 PM). Each review will consider measurements, quality of the measurements, trends, changes from baseline, and contributing factors. Patients may require follow-up telephone or in-person clinic assessment to guide management decisions, for example, with repeat high-resolution computed tomography (HRCT), 6-minute walk test, long-term oxygen therapy assessment, and laboratory-based PFTs. Patients will continue to receive standard care as per their local clinical protocols.

### Setting

Patients will be recruited from ILD specialist clinics at Guy’s and St Thomas’ NHS Foundation Trust (GSTT) and Royal Devon University Healthcare NHS Foundation Trust (RDU), from March 2022 to January 2023. All patients will have 12 months of home monitoring. Alerts will be managed by ILD specialist clinicians at each site. All clinical data will be collected on the browser-based portal and in an electronic case report form within secure Microsoft Office software only accessible to participating clinicians.

### Participants

A total of 200 patients will be recruited from 2 ILD specialist services in the United Kingdom to achieve robust and comprehensive insights from a diverse patient population. Adhering to the inclusion and exclusion criteria, ILD specialist clinicians will recruit adults aged 18 years and older, with a tertiary center multidisciplinary diagnosis of ILD confirmed by HRCT and expectation of variability in progression. Patients will need to be able to perform spirometry and achieve a baseline FVC >45% predicted value within 6 months of recruitment. They will need access and the ability to use a smart device with internet and email. A budget will be available to provide smart devices and internet connectivity to patients who do not have access. Patients will need to be able to communicate with the team, understand written instructions, and complete PRMs. Patients will not be able to participate if they have a life expectancy of less than 6 months determined by clinical judgment, contraindications to spirometry as per Association for Respiratory Technology and Physiology guidelines, upper or lower respiratory tract infection within 4 weeks, acute exacerbation within 4 weeks, and active cancer diagnosis or life-limiting malignancy [36].

All patients will have 3 monthly virtual reviews with an ILD specialist clinician. Home monitoring measurements will be reviewed. Patients will be asked to report any upper or lower respiratory tract infections, acute exacerbations, accident and emergency presentations, or hospital admissions in the previous 3 months. Responses will be documented on the browser-based portal and electronic case report form. Daily alerts will be reviewed and addressed by the clinical team. Alert management will be documented on the browser-based portal and electronic case report form. Patients who miss weekly measurements for 3 weeks or choose to withdraw from home monitoring will be contacted, and the reason for stopping will be documented on the browser-based portal.

### Variables

The variables to be measured and how they will be measured are outlined in Table 1.

**Table 1 table1:** Outcome measures.

		Measurement tools
**Primary outcome measures**		
	Potential to detect disease progression, acute exacerbation, or response to treatments enabling prompt review of patients and access to appropriate therapies compared with standard care	Browser-based portal: Number of patients with ≥5%-10% decline in FVC^a^ Time to ≥5%-10% decline in FVC Number of patients diagnosed with progressive pulmonary fibrosis who become eligible for antifibrotic treatment PRM^b^ changes in score Number of patients who start or change their prescription for oxygen therapy Time to titrate or start oxygen therapy Electronic case report form: Number of acute exacerbations and how they were managed Interventions made (type and number)
	Impact on the number of in-person clinic consultations with ILD^c^ clinicians compared with standard care	Electronic case report form: (data comparison with 2019 to 2020): Number of F2F^d^ consultations Number of telephone consultations Number of video consultations
	Impact on the number of laboratory-based pulmonary function tests compared with standard care	Electronic case report form (data comparison with 2019 to 2020): Number of F2F consultations Number of telephone consultations Number of video consultations
	Real-world patient acceptability of home monitoring program, including spirometry, oximetry, and PRMs	Browser-based portal: Frequency of patient recording of key measurements (eg, spirometry, pulse oximetry, PRMs) Duration (minutes) of regular patient engagement with the application Patient engagement and experience measure ratings Electronic case report form: Patients not eligible or declined participation and reason

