### Quantitative Variables

Statistical analysis will include patient demographic data, including age, gender, ethnic background, smoking status, occupation and geographical location, measurements and PRM responses, number and type of alerts and interventions, number and mode of clinic consultations, and investigations.

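### The detection primary outcome is measured by events that are never tied to a preceding alert or other home-monitoring flag, so as written it cannot separate detected from missed exacerbations or show the false-alert burden

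*Protocol article*

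**What the plan says.** **The outcome.** In the protocol article (Methods, Variables, Table 1), the first primary outcome reads in full: "Potential to detect disease progression, acute exacerbation, or response to treatments enabling prompt review of patients and access to appropriate therapies compared with standard care".

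**Its measures.** From the portal: "Number of patients with ≥5%-10% decline in FVC", time to that decline, patients who become eligible for antifibrotic treatment, change in patient-reported scores, and oxygen starts or changes with their timing. From the electronic case report form: "Number of acute exacerbations and how they were managed Interventions made (type and number" (a closing bracket follows).

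**The alert system.** In the text after Figure 1 (Study Design), the registering clinician is responsible for "setting thresholds for a ≥10% decline in absolute forced vital capacity (FVC) and oxygen saturation <94" per cent, according to the individual's baseline. Then: "If measurements fall below the threshold, alerts will be sent to the clinical team via the browser-based portal". The team reviews alerts on weekdays.

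**Records kept.** Under Participants: "Alert management will be documented on the browser-based portal and electronic case report form". The same section has patients report exacerbations and admissions from the preceding 3 months at each virtual review.

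**Use of alerts in the analysis.** Table 1 mentions alerts once, as a secondary measure of the time taken to deal with each. Quantitative Variables adds "number and type of alerts and interventions". Statistical Methods plans descriptive summaries and compares home with hospital spirometry at baseline only.

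**The concern.** Detection is a relation between two things: an event, and a signal that came before it. Row 1 records events and their consequences; alerts are tallied elsewhere. Nothing in the article ties an exacerbation to an earlier alert or other home-monitoring flag, or an alert to what followed.

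An exacerbation recalled at a quarterly review adds one to the count, and so does one that an alert brought to light. A high count may mean good detection, poor detection or a sick population.

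This is separate from the question of a standard-care comparator. Even with a perfect control group, events caught and events missed among the monitored patients would stay mixed together.

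At stake is what the study can tell others. The Discussion intends the results to inform adoption of home monitoring and a digital care pathway. A service deciding on adoption needs to know what share of exacerbations were flagged in time and what share of alerts led nowhere.

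**Working it through.** The article gives no event rate, alert rate or power calculation for this outcome, so there is no stated figure to reproduce. The check has three steps.

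**1. Does any measure carry the link?**

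| Item | Where | Tied to a flag? |
|---|---|---|
| FVC decline, number and time | Table 1, row 1 | No |
| Antifibrotic eligibility; oxygen starts, changes, timing | Table 1, row 1 | No |
| Change in patient-reported scores | Table 1, row 1 | No |
| Exacerbations and their management; interventions | Table 1, row 1 | Not stated; management notes may mention an alert |
| Time to deal with each alert | Table 1, secondary | Alert only, no event |
| Number and type of alerts and interventions | Quantitative Variables | Totals only |

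FVC does not fill the gap. A decline of 5% to under 10% can count in the outcome without reaching the stated FVC alert level; the two passages need to be reconciled. A home decline of 10% or more comes from the same readings that raise the alert, so its link to an alert holds by construction and says nothing about accuracy.

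**2. What can separate totals show?** Let N be patients, E patients with an exacerbation and A patients with an alert. If only these totals are known:

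- share of exacerbation patients alerted: from max(0, A+E−N)/E to min(A, E)/E
- share of alerted patients with an exacerbation: from max(0, A+E−N)/A to min(A, E)/A

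N = 200 is the planned size (Participants). E and A are assumptions. Even at the largest values, A+E−N = 120+60−200 = −20, so every lower bound is 0.

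| E | A | Exacerbation patients alerted | Alerted patients with exacerbation |
|---|---|---|---|
| 20 | 40 | 0–100% | 0–50% |
| 20 | 80 | 0–100% | 0–25% |
| 20 | 120 | 0–100% | 0–17% |
| 40 | 40 | 0–100% | 0–100% |
| 40 | 80 | 0–100% | 0–50% |
| 40 | 120 | 0–100% | 0–33% |
| 60 | 40 | 0–67% | 0–100% |
| 60 | 80 | 0–100% | 0–75% |
| 60 | 120 | 0–100% | 0–50% |

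With the 186 patients actually recruited, the pattern is the same. These bounds ignore timing: requiring the alert to come first can only lower the true shares.

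**3. What would linking give?** The margin at an alerted proportion of 50% is 1.96 × √(0.5 × 0.5 / n), for n exacerbations (assumed):

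- n = 10: 1.96 × √0.025 = 0.310, about ±31 points
- n = 20: 1.96 × √0.0125 = 0.219, about ±22 points
- n = 40: 1.96 × √0.00625 = 0.155, about ±15 points
- n = 60: 1.96 × √0.004167 = 0.127, about ±13 points

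This treats exacerbations as independent; repeat events in the same patient would usually widen it.

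**The case against.** The strongest reply is that the article condenses a fuller protocol, that Table 1 lists variables and data sources rather than derivations, and that matching rules belong in an analysis plan. That stands for the length of a matching window or the coding of an alert, and neither is criticised here. It does not cover the measures themselves. The article fixes them for a primary outcome named as detection, and an analysis of those measures alone would inherit the mismatch.

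Four stronger readings are tempting, and the documents support none of them.

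- *Row 1 holds only counts and times.* It also has change in patient-reported scores and a description of how exacerbations were managed.
- *A rule that missed every exacerbation would give the same primary result as one that caught them all.* That is true of the exacerbation count alone. Management, interventions and oxygen timing could differ between caught and missed events, so there is some indirect information.
- *Detection means alerts.* Study Design gives clinicians real-time sight of all data and has them consider trends, and Participants adds 3-monthly review of home measurements. Something noticed there without an alert is still detection by home monitoring.
- *The study cannot answer the question.* The limit lies in the outcome as written. Alert management is recorded on the portal and the case report form, so linkage looks feasible.

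It is also fair to say that the programme does not set out to validate alert thresholds, and that number, type and handling time cover part of the alert burden. They do not show what share of alerts was followed by anything.

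**Conclusion.** The concern holds in a limited form. The measures fixed for the first primary outcome do not show whether home monitoring flagged an event beforehand. As written, the outcome cannot separate detected from missed exacerbations, nor give a false-alert proportion; management and intervention records bear on this only indirectly.

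Size: for eight of the nine assumed combinations, separate totals leave the alerted share of exacerbation patients wholly undetermined; in the ninth they only cap it at 67%. Linked records would estimate it to within about ±31 points at 10 exacerbations and ±13 at 60, taking 50% as the true share. The event and alert totals are assumptions throughout. That separate totals do not fix the overlap follows from how the outcome is defined; the assumed totals affect only the width of the bounds.

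**What to change.** Before results are reported, add two measures to row 1 of Table 1 by linking the existing alert log to the case report form event records:

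- **(a) From event back to flag.** The proportion of acute exacerbations and ILD-related admissions preceded by an alert or other home-monitoring flag within a prespecified window, with the time from alert to clinical review.
- **(b) From alert forward to outcome.** The proportion of alerts, by type (FVC or oxygen saturation), followed by a recorded event or an intervention, against those closed with no action.

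Take event dates from existing case report form and admission records. Add an onset-date field only for patients still in follow-up: 186 were recruited by January 2024 and analysis is under way, so a new field may come too late for many.

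For FVC decline, use only routinely scheduled laboratory tests as the reference. Alternatively, report it separately with two caveats: tests prompted by an alert bring verification bias, and a home decline of 10% or more triggers the alert by construction.

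If the linkage is not done, limit the conclusion to event frequency and make no detection claim.

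The cost is a record linkage, a short addition to the plan and, for some patients, one date field. The downsides are that event dates will be approximate and that the detection result may look less favourable than raw counts.

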**Secondary outcome measures**		
	Impact on clinician time and experience compared to standard care	Browser-based portal: Clinician time spent on the browser-based portal Electronic case report form: Time taken to address each alert
	Correlation of PRMs with patient symptoms	Electronic case report form: Review symptoms and measurements every 3 months
	Number of patient requests for technical support	Browser-based portal: Number and length of unique interactions with the technical team
	Impact on the number of ILD-related hospital admissions and duration of inpatient stay	Electronic case report form: Review admissions every 3 months
	Impact on patient access to ILD specialized services	Browser-based portal: Completion of PRMs Electronic case report form (data comparison with defined standard care, eg, 3-4 per year, and 2019 to 2020): Number of interactions with the ILD team
	Correlation between home monitoring and patient satisfaction	Browser-based portal: PRMs Duration and frequency of patient app use
	Impact on travel costs to the patient, NHS^e^, and environment	Electronic case report form: Postcode and usual mode of travel at registration Cost of mode of transport (car mileage 45p per mile) Dependent on carer support

^a^FVC: forced vital capacity.

^b^PRM: patient-reported measure.

^c^ILD: interstitial lung disease.

^d^F2F: face-to-face.

^e^NHS: National Health Service.

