## Discussion

### Previous Work

The incidence and prevalence of PPF and IPF are increasing [37,38]. A recent real-world study suggested that up to 20% of patients treated for PPF had advanced disease [37]. This is associated with productivity loss, increased health care costs, and reduced QoL [39]. Detecting and treating acute exacerbations early is likely to positively impact health care resource consumption, and direct or indirect costs, and enable informed choice relating to the place of death. Previous studies have demonstrated good adherence and feasibility of home monitoring in ILD, in clinical trial settings, and when observed in study populations [16,17,20,40-43]. A systematic review found that home monitoring presented an opportunity for early detection of disease progression or acute exacerbation [18]. The COVID-19 pandemic accelerated the utilization of home monitoring and supporting delivery of care closer to home [21,22].

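### Two primary outcomes claim an impact relative to standard care but are compared only with 2019 to 2020, so calendar-time change cannot be separated from the effect of home monitoring

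*Protocol article*

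**What the plan says.** In the protocol article, Methods, Variables, Table 1, the second primary outcome is "Impact on the number of in-person clinic consultations with ILD" clinicians, relative to standard care. Its data source is given as "Electronic case report form: (data comparison with 2019 to 2020". The third primary outcome, laboratory PFTs, is framed in the same way and has the same comparator: "Electronic case report form (data comparison with 2019 to 2020): Number of F2F consultations". (That this row lists consultation counts and no PFT count is a separate matter.)

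A second benchmark appears only for the secondary outcome on access to specialized services: "data comparison with defined standard care, eg, 3-4 per year, and 2019 to 2020". It is not attached to either primary row.

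There is no concurrent control. Under Study Design, "All participants will be offered a portable handheld Spirobank Smart MIR spirometer". The Setting section plans recruitment "from March 2022 to January 2023", with 12 months of monitoring for each patient. The Results section reports 186 patients recruited by January 2024.

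On the change in care between the two periods, Previous Work in the Discussion says: "The COVID-19 pandemic accelerated the utilization of home monitoring and supporting delivery of care closer to home". The Home Monitoring section of the Introduction makes a similar statement and then gives the hypothesis of a 50% reduction in both outcomes.

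**The concern.** The claim concerns what home monitoring does to clinic visits and PFTs. The right reference is therefore what the same kind of patient would have received in 2022 to 2024 under local standard care. The comparator is a different period, with a pandemic between, and the article describes that pandemic as having changed where care is delivered. A change in visits or tests between the periods mixes the effect of home monitoring with everything else that changed.

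The window itself is ambiguous. Read as two calendar years, it includes months of disrupted service, which lowers the baseline and can hide a real reduction. Read as a mostly pre-pandemic year, it credits any later move to remote care to home monitoring.

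At stake is the headline hypothesis of a 50% reduction. The Discussion expects the results to inform adoption of home monitoring and decisions by policy makers.

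**Working it through.** The article gives no rate for 2019 to 2020, no secular trend and no power calculation (the sample size is described as pragmatic), so there is no stated figure to reproduce. The steps below show how the comparison behaves under labelled assumptions.

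**Gap between periods.** On the latest reading the window ends in December 2020. January 2021 to February 2022 is 12 + 2 = 14 months before monitoring can start.

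**Decomposition.** Let R_h be the rate in the historical window, R_c the rate in the monitored months under standard care alone, and R_m the rate under monitoring. Then

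R_m / R_h = (R_m / R_c) × (R_c / R_h).

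The plan observes the left side and wishes to claim the first factor. The two agree only if R_c / R_h = 1. Nothing in the design estimates R_c.

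**Pre-pandemic window.** Suppose activity fell by a fraction s for reasons other than monitoring (assumed). The true reduction needed to observe 50% is 1 − 0.5/(1 − s):

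| s | True reduction needed |
|---|---|
| 20% | 1 − 0.5/0.8 = 37.5% |
| 30% | 1 − 0.5/0.7 = 28.6% |
| 40% | 1 − 0.5/0.6 = 16.7% |
| 50% | 1 − 0.5/0.5 = 0% |

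**Window with disrupted months.** Suppose the baseline is depressed by a fraction b and service has since recovered (assumed). A true 50% reduction appears as 1 − 0.5/(1 − b):

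| b | Apparent reduction |
|---|---|
| 10% | 1 − 0.5/0.9 = 44.4% |
| 25% | 1 − 0.5/0.75 = 33.3% |
| 40% | 1 − 0.5/0.6 = 16.7% |

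For the scale of b: if disruption began in March 2020 (assumed) and the window is two calendar years, 10/24 = 41.7% of its months are affected. A fall of 50-90% in those months (assumed) gives b = 0.417 × 0.5 = 21% to 0.417 × 0.9 = 38%. The 25% used above corresponds to a 60% fall, since 0.417 × 0.6 = 0.25. If the baseline was depressed and care also moved to remote later, the two biases partly offset and the net sign is unknown.

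**Significance.** Statistical Methods sets P<.05 but names no test for these outcomes. If two independent Poisson counts with equal person-time were compared two-sided, SE = √[1/(nr) + 1/(nr(1 − s))]. Take n = 186 to 200 patients and r = 2 to 4 visits a year, from the 3-6 monthly visits described in the Abstract. With no true effect, the chance of P<.05 is about 11-17% at s = 5%, 29-54% at s = 10% and 82-99% at s = 20%. Example: n = 186, r = 2, s = 20% gives SE = √(1/372 + 1/297.6) = 0.0778 and z = 0.223/0.0778 = 2.87, so the chance is about 82%.

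**The case against.** Several points on the other side have force.

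First, the article does not document a fall in these particular outcomes. The Home Monitoring section ties the pandemic shift to devices used to avoid admission or allow early discharge. The Abstract still describes standard care as regular hospital outpatient visits, and the Introduction says that home monitoring of ILD is not yet part of standard care. This stands: the size of the secular change is unknown. It does not rescue the comparison, because the design cannot show that the change is zero.

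Second, a reader might infer that participants and the comparator group differ in case mix, since enrolment requires FVC above 45% predicted, ability to use a smart device and freedom from recent infection or exacerbation. The article does not support this as a fact, because it does not say where the 2019 to 2020 data come from. If they are clinic-level, those criteria do create a difference. If they come from the same patients, the criteria do not make two groups; instead disease stage differs, and patients new since 2020 have no earlier record.

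Third, a reader might say that a 20-40% secular fall supplies 40-80% of the hypothesised reduction. That divides percentage points, but rates compound. On the log scale the share is ln 0.8/ln 0.5 = 32% to ln 0.6/ln 0.5 = 74%, and the fall itself is assumed.

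Fourth, this is a quality improvement project with endpoints summarized descriptively, and the Bias section promises sensitivity analyses. The descriptive purpose supports a modest remedy. The sensitivity analyses are unspecified, and the stated limitations mention only inconsistent data collection between sites, so neither addresses calendar time.

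**Conclusion.** The point holds for the second and third primary outcomes. As written, the plan would credit to home monitoring whatever else changed between 2019 to 2020 and the monitored months. A 50% reduction against that window could not be read as an effect of home monitoring, and a smaller reduction could not be read as failure.

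The structural part rests only on the document: one historical comparator, no concurrent control, a gap of at least 14 months, and the article's own account of a shift in care. The sizes (a true effect of about 38% down to 17% behind an observed 50%; a true 50% appearing as 33%) rest on assumed changes and are illustrations. The direction of bias is open until the window is defined. Confounding by case mix or stage is conditional on the source of the comparator data and should not be stated as established.

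A reader might also infer that a difference-in-differences between enrolled and non-enrolled patients should become the primary contrast. The documents do not support that: patients new since 2020 have no historical record, and for non-participants the plan logs only "Patients not eligible or declined participation and reason", not their visits, tests or FVC.

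**What to change.** 1. **Define the comparator.** State whether the historical data come from the whole clinic or from the participants themselves. Fix the window as 12 complete months before pandemic disruption; if disruption is taken to begin in March 2020, that is March 2019 to February 2020. Express consultations and PFTs as rates per patient-year. This removes the ambiguity about direction but leaves any later move to remote care in the comparison, so step 2 is also needed.

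2. **Add calendar-time context as a supporting analysis.** From existing records at both sites, extract aggregate consultation and PFT rates from 2019 through 2024, or to the end of monitoring if later. Take out participants' own counts and person-time, so that the series shows the change among patients not on home monitoring over the same months.

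3. **Limit the claim.** Report the 50% reduction as a before-after association unless the concurrent clinic rates support attribution. Add calendar time and the source of the comparator to the stated limitations.

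The article says that analysis is ongoing, so the change should be dated and, if any service-use results have been seen, labelled post hoc.

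The cost is a modest records extraction with no new patients or visits. Residual selection between participants and other clinic patients remains and must be acknowledged, and the headline claim may become less favourable.
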